### Allocation and Blinding

Participants confirmed to be eligible following the screening assessment (T0) will be invited to complete the baseline assessment (T1). Following the baseline assessment, participants will be subject to random allocation to either waitlist or treatment with the Uprise program. Block randomization will be applied in this study with a 1:1 allocation ratio using random block sizes of 4 and 6. The randomization sequence will be generated using the Sealed Envelope online randomization sequence generator [33]. Randomization and allocation of participants will be performed by a member of the trial research team ([name]). Allocation will occur within 7 days of the baseline assessment. Participants will be contacted to notify them of their allocation, with those allocated to the treatment group given instructions to access the Uprise program and those allocated to the waitlist group notified of the date for their next assessment (T2).

All outcome assessments will be completed online by participants. It is not possible to blind participants to their allocation owing to the nature of the trial design. The psychologists who provide “coaching” as part of the Uprise program will be blind to participant allocation.

### Materials

Table 1 presents the SPIRIT schedule of measures in this study. The primary outcomes will focus on the acceptability, feasibility, and safety of the Uprise program, as well as efficacy as indicated by the change in mental health symptoms (depression, anxiety, and stress). The secondary outcomes will include psychological wellbeing, quality of life, loneliness, physical health, emotion regulation, and cognitive and mindfulness processes.

Demographic variables will include age, gender, sexuality, ethnicity, work status, level of education, previously attempted university degrees, current university course load, postcode, and religion. The Lubben Social Network Scale-12 items (LSNS-12 [34]) will be used as a demographic assessment of the participants’ risk of social isolation. The Positive and Negative Affect Schedule-Trait (PANAS [35]) will be used as a measure of trait-level positive and negative affect.

**Table 1 table1:** SPIRIT schedule of enrolment, interventions, and assessments.

Variable		Study period							
		Enrolment	Baseline	Postallocation				Close out	
				Waitlist	End of waitlist	Uprise	End of treatment	3-month follow-up	
Timepoint		T0	T1	N/A^a^	T2	N/A	T3	T4	
**Enrolment**									
	Eligibility screen	Yes	No	No	No	No	No	No	
	Informed consent	No	Yes	No	No	No	No	No	
	Allocation	No	Yes	No	No	No	No	No	
**Interventions**									
	Uprise program	No	No	No	No	Yes	No	No	
	Waitlist	No	No	Yes	No	No	No	No	
**Assessments**									
	Demographic form	No	Yes	No	No	Yes	No	No	
	UCLA-LS3^b^	No	Yes	No	Yes	No	Yes	Yes	
	CES-D^c^	No	Yes	No	Yes	No	Yes	Yes	
	SIAS^d^	No	Yes	No	Yes	No	Yes	Yes	
	DASS-21^e^	No	Yes	No	Yes	No	Yes	Yes	
	PANAS^f^	No	Yes	No	Yes	No	Yes	Yes	
	K10^g^	Yes	No	No	Yes	No	Yes	Yes	
	LSNS-12^h^	No	Yes	No	Yes	No	Yes	Yes	
	ERQ^i^	No	Yes	No	Yes	No	Yes	Yes	
	FFMQ^j^	No	Yes	No	Yes	No	Yes	Yes	
	CBPQ^k^	No	Yes	No	Yes	No	Yes	Yes	
	BCIS^l^	No	Yes	No	Yes	No	Yes	Yes	
	PWB-42^m^	No	Yes	No	Yes	No	Yes	Yes	
	AQoL-8D^n^	No	Yes	No	Yes	No	Yes	Yes	
	PHQ^o^	No	Yes	No	Yes	No	Yes	Yes	
	SF-12^p^	No	Yes	No	Yes	No	Yes	Yes	
	WHO-5^q^	No	No	No	No	Yes	No	No	
	PSS-4^r^	No	No	No	No	Yes	No	No	
	Modified SDS^s^	No	No	No	No	Yes	No	No	
	Acceptability measure	No	No	No	No	Yes	No	No	
	Qualitative interview	No	No	No	No	No	Yes	No	

^a^N/A: not applicable.

^b^UCLA-LS3: UCLA Loneliness Scale Version 3.

^c^CES-D: Centre for Epidemiological Studies-Depression.

^d^SIAS: Social Interaction Anxiety Scale.

^e^DASS-21: Depression, Anxiety, and Stress Scale-21 items.

^f^PANAS: Positive and Negative Affect Schedule-Trait and State versions.

^g^K10: Kessler Scale of Distress-10 items.

^h^LSNS-12: Lubben Social Network Scale-12 items.

^i^ERQ: Emotion Regulation Questionnaire.

^j^FFMQ: Five Facet Mindfulness Questionnaire.

^k^CBPQ: Cognitive Behavioral Processes Questionnaire.

^l^BCIS: Beck Cognitive Insight Scale.

^m^PWB-42: Psychological Well-Being Scale-42 items.

^n^AQoL-8D: Assessment of Quality of Life-8 Dimensions.

^o^PHQ: Physical Health Questionnaire.

^p^SF-12: Short-Form Health Survey-12 items.

^q^WHO-5: World Health Organization-Five Well-Being Index.

^r^PSS-4: Perceived Stress Scale-4 items.

^s^SDS: Sheehan Disability Scale.

### Primary Outcomes

#### Acceptability, Feasibility, and Safety of the Uprise Program

A self-report scale created by the developers of the Uprise program and designed to measure participant satisfaction with the program will be used to determine the acceptability of the program to participants. Participants will be asked to rate out of 10 how satisfied they were with each of the program modules and coaching calls, as well as how likely they are to recommend Uprise to friends or family. Attrition rates from the trial will also be used as indicators of acceptability. Themes identified from the qualitative interviews conducted at the end-of-treatment (T3) assessment will also be used to determine acceptability of the intervention. The interview will include questions regarding the participants’ experiences and preferences regarding the different modules of the Uprise program. Feasibility will be assessed by the proportion of interested people who complete the baseline assessment, the attrition rate across both groups, and the proportion of participants who complete the four core Uprise program modules within the 6-week intervention period. Safety will be determined according to the number of adverse events occurring across the trial period.

#### Mental Health

Psychological distress will be measured with the Kessler Scale of Distress-10 items (K10 [36]). Depression will be measured with the Centre for Epidemiological Studies-Depression (CES-D [37]) and depression subscale of the Depression Anxiety Stress Scale-21 items (DASS-21 [38]). Anxiety will be measured with the anxiety subscale of the DASS-21, and social anxiety will be measured with the 20-item Social Interaction Anxiety Scale (SIAS [39,40]).

#### Stress

The Perceived Stress Scale (PSS-4 [41]) and stress subscale of the DASS-21 will be used to measure stress. The Modified Sheehan Disability Scale (modified SDS [42]) will be used to measure the effects of mental illness, physical illness, and stress on work and study.

### Secondary Outcomes

#### Wellbeing and Quality of Life

The Psychological Well-Being Scale-42 items (PWB-42 [43,44]), the World Health Organization-Five Well-Being Index (WHO-5 [45]), and the Assessment of Quality of Life-8 Dimensions (AQoL-8D [46]) will be used to measure global wellbeing and life satisfaction. The PWB measures psychological wellbeing across the following dimensions: autonomy, positive relations with others, environmental mastery, personal growth, purpose in life, and self-acceptance. The AQoL-8D measures wellbeing across the following dimensions: independent living, happiness, mental health, coping, relationships, self-worth, pain, and senses.

#### Loneliness

The UCLA Loneliness Scale-Version 3 (UCLA-LS [47]) is a 20-item self-report measure and consists of both positively and negatively worded items that assess loneliness (eg, How often do you feel that you are no longer close to anyone?).

#### Physical Health

Question 1 from the Short-Form Health Survey-12 items (SF-12 [48,49]) will be used as a single measure of health, and it asks participants to rate their perception of their overall health quality. The Physical Health Questionnaire (PHQ [50]) is a 14-item brief self-report scale of physical health symptoms.

#### Emotion Regulation, Cognitive, and Mindfulness Processes

The Emotion Regulation Questionnaire (ERQ [51]) will be used to measure participants’ tendency to use cognitive reappraisal and expressive suppression strategies to regulate their emotions. Activated affect in the past week, measured with the Positive and Negative Affect Schedule-State (PANAS-State [35]), will be used as a secondary indicator of emotion regulation. The Cognitive Behavioral Processes Questionnaire (CBPQ [52]) will be used to measure internal and external cognitive and behavioral maintenance processes. The Beck Cognitive Insight Scale (BCIS [53]) will be used to measure participants’ self-reflectiveness and self-certainty in their interpretations of their experiences. The Five Facet Mindfulness Questionnaire (FFMQ [54]) is a measure of mindfulness and comprises the following five subscales: observing, describing, acting with awareness, nonjudging of experience, and nonreactivity to experience.

### Planned Intervention

The Uprise program will be made accessible to participants as both an app and a website. Participants will complete all intervention activities online at a time and location that is convenient for them. Activities will include a series of self-directed modules and optional coaching sessions with a psychologist or counsellor.

Participants will complete four core modules over 4 to 6 weeks, with an additional six optional modules. Each module consists of a short introductory video and a series of 1 to 6 additional videos or exercises. The module length ranges from 6 to 28 minutes. The modules are mindset, personal values, mindfulness, and stress management (outlined in Table 2). To support adherence to the intervention protocol, a member of the research team will contact participants weekly to check on their progress and address any technical issues.

**Table 2 table2:** Outline of the Uprise module content.

Module		Content
**Core modules**		
	Mindset	Identifying unhelpful thinking styles and changing unhelpful thoughts.
	Personal values	Identifying values system, making behavioral choices based on values system, and scheduling activities.
	Mindfulness	Developing mindfulness skills to pay attention to and observe thoughts instead of trying to control and change them.
	Stress management	Developing stress reduction and relaxation breathing skills.
**Optional modules**		
	Helping others	Skills for managing relationships with mental health in mind.
	Perspective taking	Learning to understand the perspectives of others.
	Advanced mindset	Advanced skills in retraining thinking related to stress, guilt, metacognition, and beliefs.
	Improving sleep	Strategies to improve sleep habits.
	Advanced mindfulness	Advanced skills in awareness and mindfulness.

#### Optional Coaching Sessions

The Uprise program also provides participants with in-website links to telephone or online coaching sessions with a trained mental health professional at any point during the program. Participants will be able to choose from a list of psychologists and counsellors to select their “coach” and schedule weekly 30-minute telephone or webchat sessions with their coach. It will be up to the participant to decide whether to engage with this aspect of the program.

### Waitlist Condition

It will be clearly outlined to participants that the trial involves a waitlist control prior to enrolment, and informed consent will include agreement to undergo a 4-week waitlist period and an additional assessment prior to commencing the Uprise program. Waitlist participants will be instructed to continue with their usual activities throughout the waitlist period.

### Planned Data Analysis

Summary data will be provided to describe the number of participants who registered interest in the trial, the number deemed ineligible for the trial and why, and the number who completed each stage of the trial.

Data will be analyzed on an intention-to-treat basis (ie, including all enrolled participants regardless of whether they completed the trial). Acceptability, feasibility, and safety will be evaluated using descriptive statistics. Qualitative interviews will be analyzed using the six-step approach by Braun and Clarke [55] for qualitative data analysis to identify and develop themes from the data to further inform about the acceptability of the intervention to participants.

Results will be summarized as means and standard deviations (or median and range/percentage and number as appropriate) for both groups at baseline (T0) and for the relevant group at the end of waitlist (T2)/end of treatment (T3) for all outcome measures. For both groups, this will demonstrate their results at baseline and again 4 weeks after baseline.

Additionally, the *t* test and chi-square test will be used to evaluate baseline group differences in all demographic and outcome measures. This will be performed to compare the waitlist and intervention groups, and to compare those who drop out from the trial to those who complete the trial. This will enable identification of potential baseline moderator variables or factors that contribute to attrition that can be included as covariates in subsequent analyses.

Multilevel linear mixed effects modeling (MLM) will be used to assess acute and long-term treatment effects in each of the outcome measures. MLM is a regression-based approach that is robust to missing data and provides a more powerful means of analyzing longitudinal data than the ANOVA family of analyses [56]. MLM is robust to missing data because it does not delete cases list-wise due to missing data, but instead includes all available data points for each participant. Missing data analysis will be conducted to determine whether data are missing completely at random. If it is identified that data are missing not at random, covariates will be added to all models to account for systematic variation related to missingness.

To assess short-term treatment effects, the trajectory of change in each of the outcomes will be examined from baseline (T1) to the end of waitlist (T2) for the waitlist group and from baseline (T1) to the end of treatment (T3) for the intervention group. The trajectory of change in each of the outcomes will be compared between groups. Each analysis will include time (fixed), group (fixed), and the fixed interaction between time and group (time × group) as predictors. A significant time × group interaction effect will indicate a differential rate of change in outcomes between the groups from baseline (T1) to the end of waitlist (T2)/end of treatment (T3).

To assess long-term treatment effects, the trajectory of change in outcomes from baseline (T1) to 3-month follow-up (T4) will be examined in the intervention group only. Sensitivity analysis will also be conducted to determine the trajectory of change from baseline (T1) to 3-month follow-up (T4) in the waitlist group only.

Secondary analyses will include per protocol analysis (only those who complete the four core modules within 6 weeks) and analyses controlling for moderator variables (eg, age, sex, baseline symptom severity, number of Uprise program modules completed, number of coaching calls completed, and number of days accessing the platform). We will report 95% confidence intervals for each test statistic.

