**Methods:**

This is a pilot randomized controlled trial comparing a self-directed web-based CBT mental health program with a waitlist control. The self-directed modules will be augmented with optional webchat or telephone coaching with a therapist. The recruitment target is 70 university students who do not present with a clinical mental health disorder. Allocation will be made in a 1:1 ratio and will occur after the initial baseline assessment. Assessments will be completed at baseline, upon completion of a 4-week waitlist (waitlist group only), upon completion of the program, and at 3 months after completion of the program.

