## Methods

### Trial Design

The study will be a pilot randomized waitlist-controlled trial, with two parallel groups, using a 1:1 allocation ratio. Waitlist was selected as the control condition to enable comparison of the Uprise program to students’ usual daily life, while ensuring that all participants had the opportunity to access the Uprise program. Figure 1 presents the study design.

Participants will initially undergo screening for eligibility via telephone interview (T0). Eligible participants will be invited to complete the baseline assessment (T1). Informed consent will be obtained at the baseline assessment. Following the baseline assessment, each consenting participant will be randomized to either the Uprise program or waitlist for the following 4 weeks. Those allocated to the Uprise program will be given access to the program and asked to complete one module per week across the following 4-week period. At the end of the program, these participants will be invited to complete an end-of-treatment assessment (T3). Participants allocated to waitlist will be asked to continue with their usual activities across the following 4-week period, at the end of which they will be invited to complete an end-of-waitlist assessment (T2). Waitlist participants will then be given access to the Uprise program and asked to complete one module per week for the following 4 weeks, at the end of which they will be invited to complete an end-of-treatment assessment (T3). Participants will also be invited to complete a semistructured interview at the end-of-treatment (T3) assessment regarding their experience with the intervention. The interview will be recorded and later transcribed for qualitative analysis. All participants will be invited to complete a follow-up assessment (T4) 3 months after their end-of-treatment (T3) assessment.

The Consolidated Standards of Reporting Trials (CONSORT) flow diagram of the study procedure is shown in Figure 1. The protocol was designed in accordance with the Standard Protocol Items: Recommendations for Interventional Trials (SPIRIT) and good clinical practice (GCP) guidelines (see Multimedia Appendix 1 and Multimedia Appendix 2 for relevant checklists).

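### The short-term comparison is said to show both arms 4 weeks after baseline, but the protocol's own timing allows the Uprise assessment to fall up to 2 weeks later than the waitlist one

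*Protocol article*

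**What the plan says.** The protocol article fixes the waitlist clock consistently. Trial Design states: "Participants allocated to waitlist will be asked to continue with their usual activities across the following 4-week period", with T2 at the end of that period. Waitlist Condition agrees: "informed consent will include agreement to undergo a 4-week waitlist period and an additional assessment prior to commencing the Uprise program".

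The Uprise clock is less settled. The abstract's Methods list the later assessments as "upon completion of a 4-week waitlist (waitlist group only), upon completion of the program, and at 3 months after completion of the program", so T3 is triggered by completing the program. Trial Design likewise invites Uprise participants to T3 when the program ends. The length of the program varies by section:

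- Trial Design: a module a week over 4 weeks.
- Planned Intervention: "Participants will complete four core modules over 4 to 6 weeks".
- Acceptability, Feasibility, and Safety of the Uprise Program, as a feasibility measure: "the proportion of participants who complete the four core Uprise program modules within the 6-week intervention period".
- Planned Data Analysis, per-protocol definition: four core modules finished inside 6 weeks.

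The efficacy contrast in Planned Data Analysis sets the change from T1 to T2 in the waitlist arm against the change from T1 to T3 in the Uprise arm, through a time-by-group interaction. The same section describes the summaries of these assessments thus: "For both groups, this will demonstrate their results at baseline and again 4 weeks after baseline".

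**The concern.** A two-arm comparison of change is clean when both arms are measured at the same distance from randomization. Here one arm is measured when a fixed wait ends. The other is measured at an event whose date, on several of the passages, can move with the participant's pace through the modules.

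If T3 does run later, the interaction contains more than the program effect. It also picks up any change that would have happened anyway in the extra time, such as natural change, the academic calendar or regression to the mean. Change in mental health symptoms is one of the primary outcomes, so the sentence that fixes when the arms are compared has to be one the rest of the text supports.

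**Working it through.** **1. Testing the stated figure: 4 weeks after baseline in both arms.**

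Allocation and Blinding allows allocation up to 7 days after baseline. Taking the wait, or access to the program, to start at allocation:

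| | Weeks from allocation | Weeks from baseline (adding 0 to 1) |
|---|---|---|
| Waitlist T2 | 4 | 4 to 5 |
| Uprise T3, 4-week program | 4 | 4 to 5 |
| Uprise T3, 4-to-6-week program | 4 to 6 | 4 to 7 |

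The figure is exact only if allocation falls on the day of baseline and T3 is sent at 4 weeks. The allocation delay applies to both arms, so it makes the figure inexact but creates no difference between them. The difference comes from program length: 6 − 4 = 2 weeks at most, and 2/4 = 50% longer follow-up.

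**2. What the gap does to the interaction.**

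Let *b* be a weekly change (in SD) common to both arms, *δ* the program effect, and *w*U and *w*W the weeks of follow-up. With time treated as occasion (before, after), which is an assumption because the article does not state the coding:

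- waitlist change = *b* × *w*W
- Uprise change = *δ* + *b* × *w*U
- interaction = *δ* + *b* × (*w*U − *w*W)

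The second term is the distortion. It depends on the average gap in the Uprise arm, not on the largest one.

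**3. Size.**

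The article gives no drift rate, so 0.01 to 0.10 SD per week is assumed. The planning effects in Sample Size are *d* = 0.43 to 0.57.

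| Average gap | Drift 0.01 per week | Drift 0.05 per week | Drift 0.10 per week |
|---|---|---|---|
| 0 weeks | 0 | 0 | 0 |
| 1 week | 0.01 SD | 0.05 SD | 0.10 SD |
| 2 weeks (everyone at the maximum) | 0.02 SD | 0.10 SD | 0.20 SD |

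As a share of the planning effects, the range runs from 0.01/0.57 = 2% to 0.20/0.43 = 47%. The middle case (1 week, 0.05 per week) is 0.05/0.57 = 9% to 0.05/0.43 = 12%.

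**4. Effect on the test.**

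This uses 35 per arm, an assumed two-sided 0.05 level, a normal approximation and a comparison of post-scores. SE = √(2/35) = 0.239 SD.

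- Distortion 0.10 SD: 0.10/0.239 = 0.418. Type I error = [1 − Φ(1.960 − 0.418)] + Φ(−1.960 − 0.418) = 0.062 + 0.009 = 0.070.
- Distortion 0.05 SD: type I error 0.055.
- With an assumed baseline correlation of 0.7, SE is multiplied by √(1 − 0.49), and the two figures become 0.090 and 0.060.
- With no gap: 0.050.

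**The case against.** The best reply is that Trial Design can be read as giving everyone a 4-week T3. It randomizes to Uprise or waitlist for 4 weeks, asks for a module a week over that time, and then places T3. Read with the disputed sentence, the arms are aligned, and 6 weeks is only a completion threshold for feasibility and the per-protocol set. This reading is available and cannot be excluded. The abstract and Planned Intervention point the other way, so the text is ambiguous. If 4 weeks was the practice, the confounding disappears and only the contradictory wording remains.

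A reader might also infer that tying T3 to completion leaves slow users and non-users without a T3, against the intention-to-treat aim. The article does not support that. Nothing in it withholds T3 from non-finishers, everyone enrolled is to be analysed, and research staff make weekly contact. What happened to non-finishers is simply not stated, and an article may leave such detail to the full protocol. Nor does intention to treat itself demand a fixed-time assessment, since it governs who is analysed and in which arm. Fixed timing is the better design choice on other grounds.

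The size is also open to challenge, and rightly. The drift is assumed, it need not be linear over weeks 4 to 6, and the 2-week row puts every Uprise participant at the maximum. The direction is not known either. Eligibility Criteria exclude Kessler scores of 25 or more, so regression to the mean could raise distress and count against Uprise.

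**Conclusion.** The contradiction is firm: the article states a common 4-week timing that its own account of program length and T3 does not assure. Whether the arms were actually followed for different times is not established. It would be tempting to conclude that treatment is confounded with elapsed time and with finishing the modules. The documents support only the conditional statement: unless T3 went to everyone at 4 weeks, follow-up may be 0 to 2 weeks longer in the Uprise arm, and the interaction then mixes program effect with elapsed time.

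The range of 0.01 to 0.20 SD rests on the assumed drift, an average gap of 1 to 2 weeks and time coded as occasion. It is an illustration, not an estimate of bias. The point should be fixed before the efficacy result is interpreted. Confidence is moderate.

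**What to change.** **In the plan.** Reconcile the passages on program length and on the timing of T3. Which length applies is for the sponsor to settle. Define the short-term outcome at the same time from allocation in both arms, with the same window, regardless of modules completed. The cost is small: some Uprise participants would be assessed before finishing.

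**For the data in hand.** The Results section puts the end of data collection at December 2019, so the assessments cannot be moved. Before the final analysis is reported:

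- State what triggered T3, including for participants who did not finish.
- Correct or delete the sentence on 4-week timing if it does not hold.
- Report the distribution of days from allocation to T2 and T3 by arm.

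This costs a few lines of text and one descriptive table.

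**Sensitivity checks only.** A model with elapsed days, or an analysis limited to a common window, may be added, with a note that it conditions on post-randomization behaviour. If T3 followed completion, days in the Uprise arm reflect module pace and overlap heavily with arm, and a common window selects faster finishers. Neither should replace the main analysis.

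### The main short-term model is in effect a change-score analysis: valid, but less precise than adjusting for the baseline score already collected, and the baseline significance tests do not make up the difference

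*Protocol article*

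**What the plan says.** Three statements under Planned Data Analysis bear on this.

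- **Main short-term model.** "Each analysis will include time (fixed), group (fixed), and the fixed interaction between time and group (time × group) as predictors". The waitlist arm contributes T1 and T2 and the intervention arm T1 and T3, so each participant has one baseline and one later value. The treatment effect is read from the interaction: "A significant time × group interaction effect will indicate a differential rate of change in outcomes between the groups". No adjustment for the baseline score and no equal-baseline constraint is given.
- **Baseline tests.** A t test or "chi-square test will be used to evaluate baseline group differences in all demographic and outcome measures", both between the randomised arms and between dropouts and completers. Their purpose is stated: "This will enable identification of potential baseline moderator variables or factors that contribute to attrition that can be included as covariates in subsequent analyses".
- **Baseline severity.** It appears as a variable to control for only in the secondary analyses, next to age, sex and measures of programme use.

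Sample Size gives d = 0.43 to 0.57 and a recruitment ceiling of 35 per arm set by funding.

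**The concern.** The group term is free at baseline, so the model estimates a separate T1 mean in each arm even though randomisation makes the two expected means equal. With one follow-up point, that reduces the interaction to a comparison of raw changes. A change score subtracts the whole baseline value, whereas the efficient adjustment subtracts only the fraction r of it. The surplus adds noise.

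The plan prefers mixed models partly because they are more powerful than ANOVA methods. In a two-point contrast with complete data, that advantage does not arise.

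The baseline tests may look like a safeguard. Between randomised arms, however, any difference is due to chance, so the tests say nothing about whether allocation worked. A flagged variable entered as a covariate would also not correct the interaction. At stake is precision in a trial whose numbers can no longer grow: the Results section reports recruitment closed at 70, with the final analysis still ahead.

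**Working it through.** **Inputs.** From Sample Size: 35 per arm, d = 0.43 and 0.57. Assumed because the document does not state them: two-sided alpha 0.05, no dropout, d on the raw-score SD, equal SD σ at both times, and r from 0.3 to 0.8.

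**The plan's own figure.** The 27 to 45 per group is reproduced by a paired t test within one group at 80% power: 26.1, rounded up to 27, for d = 0.57, and 44.4, rounded up to 45, for d = 0.43. A two-group t test on the same d needs 50 and 86 per arm. That is a separate matter. Here it means only that the stated range cannot serve as the power of the between-arm interaction, so power is computed directly.

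**Step 1: the interaction is a change-score difference.** In a simulated complete data set with 35 per arm, the mixed-model interaction was −0.4371 (SE 0.1902). The difference in mean change was −0.4371 (SE 0.1902).

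**Step 2: an added covariate does not alter it.** Adding a baseline covariate as a main effect to that model again gave −0.4371 (SE 0.1902). A time-constant covariate shifts a participant's two values equally and cancels from the change. With 20% random dropout and r = 0.5 (60 simulated data sets, one covariate), the mean absolute shift was 0.02 SD against an SE of 0.26.

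**Step 3: variance.**

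- Change: (2σ²/n) × 2(1 − r)
- Baseline-adjusted: (2σ²/n) × (1 − r²)
- Ratio: (1 − r²) / [2(1 − r)] = (1 + r)/2

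**Step 4: power at 35 per arm.** The noncentrality is d√(35/2) divided by √[2(1 − r)] for change or √(1 − r²) for the adjusted analysis. For d = 0.43 and r = 0.5, this is 0.43 × 4.183 / 1 = 1.80 for change (power 43%) and 0.43 × 4.183 / 0.866 = 2.08 adjusted (53%).

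| r | Variance ratio | d = 0.43, change → adjusted | d = 0.57, change → adjusted |
|---|---|---|---|
| 0.3 | 0.65 | 32% → 46% | 51% → 69% |
| 0.5 | 0.75 | 43% → 53% | 65% → 77% |
| 0.7 | 0.85 | 63% → 70% | 86% → 91% |
| 0.8 | 0.90 | 80% → 84% | 96% → 97% |

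At r = 0.5 the saving equals 1/0.75 = 1.33 times the participants, about 47 per arm instead of 35. At r = 0.8 it equals 1/0.90 = 1.11 times, about 39 per arm.

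**Step 5: behaviour under chance imbalance.** In simulated null trials at 35 per arm, the change analysis rejects 5.0% of the time overall. Among the roughly one in twenty trials in which the outcome itself differs significantly at baseline, it rejects about 16% to 19% of the time at r = 0.5 and 11% to 14% at r = 0.7, over repeated simulation runs. The baseline-adjusted analysis stays near 5% in those same trials.

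**The case against.** The strongest reply is that nothing in the planned model is wrong. Under randomisation the change analysis is unbiased, its overall type I error is 5%, and the baseline does enter, as a response. The trial is a pilot in which acceptability, feasibility and safety are also primary and are described rather than tested. The size of the gain rests on an r that the document does not give: at r = 0.8 and d = 0.57 it is about one percentage point. All of this stands. It makes the point one of efficiency, not of error.

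Two stronger readings are tempting, and the document supports neither.

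- A reader might infer that the reported effect will depend on which chance imbalances happen to be significant. The text says only that variables can be included, gives no threshold, and lists the analyses controlling for moderators as secondary. A covariate entered as a main effect also leaves the interaction where it was (Step 2). The estimate would move materially only if covariates were also interacted with time, which is not planned.
- A reader might fault the comparison of dropouts with completers on the same ground. Dropout is not randomised, so differences there are not chance by design. Describing them, and conditioning on predictors of dropout, is a reasonable way to make a missing-at-random assumption more plausible.

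The reply does not justify the between-arm tests, and it does not explain why the less precise of two valid analyses of the same data should be the main one.

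**Conclusion.** The point holds as a loss of precision. With complete data the main short-term model is a change-score analysis, with 1.11 to 1.54 times the variance of a baseline-adjusted one for r between 0.8 and 0.3. Adjustment would add roughly 1 to 18 percentage points of power at 35 per arm, depending on r and d, and it is better in every case examined.

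The power figures rest on the assumptions listed in the working. The variance ratio depends only on r and on equal SDs at the two times. With missing follow-up values the change-score identity is approximate rather than exact.

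The between-arm baseline tests are uninformative and do not protect against imbalance. In the very case that they would flag, an imbalance in the outcome itself, the planned analysis has inflated conditional error and the adjusted one does not. None of this makes the planned analysis biased or its overall error rate invalid.

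**What to change.** 1. For each outcome with a value before randomisation, make the main short-term analysis a mixed model with a common baseline mean in both arms (time and time × group, no group main effect at baseline). ANCOVA of the T2/T3 score on that outcome's own baseline is the alternative. Baseline is T1, or T0 for the K10, which Table 1 schedules at screening. The mixed model fits the intention-to-treat aim better, because it keeps participants who have a baseline but no follow-up value.
2. Enter the outcome's own baseline in one of these two ways. Adding it as a main effect to the existing time × group model would change nothing.
3. Drop the significance tests between arms at baseline and report baseline characteristics descriptively.
4. Keep the comparison of dropouts with completers, as a description of attrition and as support for the missing-data model.

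Table 1 shows no T1 value for the WHO-5, PSS-4 and modified SDS, so the change cannot apply to them as scheduled. The planned T1-based model has the same limit there.

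The cost is a change of analysis wording, to be recorded before the data are analysed. No new data, participants or software are needed.
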